#### Body image and cosmesis

To evaluate differences in postoperative body image and cosmesis, the Body Image Questionnaire (BIQ) will be used [43,44], which consists of eight questions about body image and cosmesis. The body image assessment will be performed preoperatively at time of consent. Both the body image and cosmesis assessment will take place at discharge, and at 10 days, 3 months, 6 months and 12 months after discharge.

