### Study design

The ORANGE II trial is a prospective superiority study with an experimental design, using two double-blinded randomised controlled arms and a prospective registry to determine whether laparoscopic surgery is to be preferred over open surgery in patients undergoing a LLS and participating in an enhanced recovery programme. In the participating randomising centers, patients, nurses and the ward physician (but not the operating surgeon) will be blinded for the type of intervention up to and including postoperative day (POD) 3. They will record the functional recovery criteria twice daily. Only the investigator and operating surgeons will know the actual procedure. The blinded ward physician(s) will decide on whether a patient will be discharged or not.

However, randomisation of patients undergoing open or laparoscopic liver resection is hazardous as previously explained. Moreover, another potential source of bias exists when randomising patients with a strong treatment preference. When patients cannot be blinded to their treatment allocation (POD 3) they may be resentful and demoralised if they do not receive their preferred treatment, and consequently they may have poor compliance. By contrast, patients receiving their preferred treatment may have above-average compliance.

Thus to capitalise on centres both with and without preference for laparoscopic liver surgery, and thereby to acquire an uninterrupted prospective series of patients, all non-randomised patients undergoing a LLS will be approached to participate in the prospective registry. Registration of these patients is imperative to guarantee a consecutive series of patients and also because the absence of such a series may restrict generalisation of the results, as randomised participants may not in fact be representative [36]. The combination of an RCT and a prospective registry will improve overall power and strengthen the external validity and generalisability of study results [33-35]. This non-randomised registry group will be analysed for centre and centre by treatment interaction as an observational study. Medical centres that wish to participate in this trial, but with liver surgeons early in the laparoscopic learning curve, will be accompanied during the procedure by an experienced proctoring laparoscopic HPB-surgeon.

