### Functional recovery criteria

The evaluation of time to functional recovery will start on POD 0 and will be scored twice daily until discharge from the hospital. The discharge process starts at the pre-admission counseling session, during which any special needs of the patients will be determined (for example, homecare or social support, transport. Before admittance, any problem that could delay discharge will be identified and addressed. Patients will only be discharged when they have met the functional recovery criteria and are willing to go home. Reasons to delay discharge after functional recovery will be monitored and documented. Functional recovery criteria and LOS in hospital will be independently monitored and analysed.

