#### Descriptive statistics

The primary outcome parameter of time to functional recovery and the secondary parameter of LOS in hospital will be given in days, with a median and range. Morbidity will be classified according to the classification described by Dindo *et al*. and defined as a dichotomous composite endpoint, while readmission will be given as a percentage. Scores for quality of life, body image and cosmesis will be given as mean and standard deviation per time point per treatment arm. Hospital costs will be given as median and range. Long-term incidence of incisional hernia will be reported and analysed.

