#### Univariate analysis

The primary outcome measure of time to functional recovery will be measured in days, and will be analysed with fixed-effect regression that will take centre and treatment × centre interaction into account as fixed effects. If the actual number of centers and the sample size per centre allow random effects analysis, this will also be performed and this analysis will have the same power as the planned fixed effects analysis if the design effect does not exceed 1.2. With a sample size of 10 patients per centre, the design effect is 1.2 if the intraclass correlation (ICC) is 0.02, where the ICC is based on treatment × centre interaction [57].

All secondary outcomes as measured at discharge will be analysed by fixed-effect regression using linear regression for quantitative outcomes and logistic regression for binary outcomes, and including the baseline measure as a covariate to improve power and precision. In addition to *P*-values, confidence intervals for all effects will be reported. Morbidity will be classified as described by Dindo *et al*., but will be presented as raw data only because the required sample size for intervention effects on morbidity is much larger than the calculated sample size for this trial [58].

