It is well recognised that a well-conducted double-blind RCT provides the highest level of evidence to prove the possible benefits of laparoscopic liver resection. However, performing an RCT in surgery is not without difficulties, and alternative trial designs may be necessary [33,34,62]. First, the intervention needs to be tested in a standardised environment, and the properties of the intervention should remain unchanged during the trial period. This seems impossible for an intervention such as laparoscopic liver surgery in a multicentre RCT. Experience varies between participating centres, and will vary over time. Moreover, local standards for perioperative care are different. Both LLS and the ERAS® enhanced recovery protocol provide the standardisation needed. The learning curve of a LLS is short in centres with experience in liver surgery and advanced laparoscopy. The use of proctor surgeons in centres with limited experience in laparoscopic liver surgery the operative techniques can be reasonably standardised, and this should eliminate learning curve influences on outcome parameters. Quality of the surgery can be assured by digital video recording.

Second, the intervention should be double-blinded. Although double blinding in a surgical trial is difficult, using a fixed abdominal dressing for 3 days after surgery is feasible, and should prevent both ward caregivers and patients from knowing the type of intervention.

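### Cosmesis is regressed on its discharge score, but a patient discharged by POD 3 may not yet have seen the wound unless the stated blind is broken early

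*Protocol article*

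**What the plan says.** Four parts of the Protocol article meet here.

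- **Timing of the score** (Body image and cosmesis): "Both the body image and cosmesis assessment will take place at discharge, and at 10 days, 3 months, 6 months and 12 months after discharge". Before surgery only one of the two is taken: "The body image assessment will be performed preoperatively at time of consent".
- **Analysis** (Univariate analysis): "All secondary outcomes as measured at discharge will be analysed by fixed-effect regression using linear regression for quantitative outcomes", with the baseline measure added as a covariate. The section on descriptive statistics covers all readings: "Scores for quality of life, body image and cosmesis will be given as mean and standard deviation per time point per treatment arm".
- **Blinding** (Study design): patients, nurses and the ward physician "will be blinded for the type of intervention up to and including postoperative day (POD) 3". The Discussion gives the means: "using a fixed abdominal dressing for 3 days after surgery is feasible, and should prevent both ward caregivers and patients from knowing the type of" operation.
- **Discharge** (Functional recovery criteria): "Patients will only be discharged when they have met the functional recovery criteria and are willing to go home". No minimum stay is stated.

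The article does not say what happens to the dressing of a patient who leaves by POD 3, or whether the questionnaire is completed before or after it comes off.

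**The concern.** A cosmesis score is meaningful only if the patient has seen the wound. The blind is meant to stop the patient learning the type of operation until POD 3 has passed. A patient discharged within that period therefore either may score a wound not yet seen or has the blind lifted early. Patients discharged later can score a visible incision. The regression treats all these scores as one outcome.

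The trial expects laparoscopic patients to leave sooner, so any affected scores would fall more often in that arm. Cosmesis is a named secondary endpoint, and the discharge comparison is the one the article selects for formal analysis.

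A smaller point sits beside it. The model calls for a baseline covariate, but no cosmesis score is taken before surgery.

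**Working it through.** **1. The conflict in the text.** This step needs no arithmetic. Discharge on or before POD 3 is allowed, the cosmesis form is due at discharge, and the patient is to be blinded up to and including POD 3. All three can hold only if the form is completed without knowledge of the wound.

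**2. Inputs for its size.** From Sample size: mean stay 6 days, SD 2.73, a 2-day reduction, 55 per arm. From the Background: a 7-day against 5-day comparison for laparoscopic surgery within ERAS. Assumptions made here: the 6-day mean is the open arm, so the laparoscopic mean is 6 − 2 = 4; both arms share the SD; the 7 and 5 days are treated as means with the same SD; the shape of the distribution is unknown, so three are tried.

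**3. The plan's own figure.** n per arm = 2 × (1.96 + 1.2816)² × (2.73/2)² = 39.2, rounded up to 40, as stated. With 10% withdrawal, 40/0.9 = 44.4, so 45. Adding 10 per arm for 10 centres gives 55 per arm and 110 in total, as stated. The inputs are therefore read as the plan reads them.

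**4. Share discharged by day c.** Normal: Φ((c − mean)/SD).

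- Laparoscopic, c = 3: Φ((3 − 4)/2.73) = Φ(−0.366) = 35.7%.
- Open, c = 3: Φ((3 − 6)/2.73) = Φ(−1.099) = 13.6%.

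The gamma (shape (mean/SD)², scale SD²/mean) and the lognormal (log-variance ln(1 + (SD/mean)²)) are matched to the same mean and SD.

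| Mean stay, open vs laparoscopic | Cut-off (days) | Normal | Gamma | Lognormal |
|---|---|---|---|---|
| 6 vs 4 | 3 | 13.6% vs 35.7% | 11.4% vs 43.3% | 8.4% vs 43.8% |
| 6 vs 4 | 2.5 | 10.0% vs 29.1% | 6.4% vs 34.4% | 3.6% vs 32.6% |
| 6 vs 4 | 3.5 | 18.0% vs 42.7% | 17.6% vs 51.6% | 15.3% vs 53.7% |
| 7 vs 5 | 3 | 7.1% vs 23.2% | 3.9% vs 25.1% | 2.0% vs 22.8% |
| 6 vs 5 | 3 | 13.6% vs 23.2% | 11.4% vs 25.1% | 8.4% vs 22.8% |

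The 2.5-day cut keeps roughly those who leave by POD 2, where the conflict cannot be put down to the hour of dressing removal. The 3.5-day cut counts the whole of POD 3 and is the most generous. If the SD shrinks with the mean (SD 1.82 at 4 days), the laparoscopic share by day 3 is 29-33%. If stay does not differ between arms, there is no imbalance.

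**5. In patients.** At 6 vs 4 days and c = 3, multiplying by 55 gives about 20-24 laparoscopic and 5-8 open patients. At 7 vs 5 days it gives about 13-14 and 1-4. The 55 includes the allowance for withdrawal, so the numbers with data would be somewhat smaller.

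**6. Baseline.** The preoperative assessment covers body image only, so the covariate named in Univariate analysis does not exist for cosmesis.

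**The case against.** The dressing is mentioned only in the Discussion, as a remark on feasibility. Study design does not mention it. The blind chiefly protects the recovery scores and the discharge decision, both made by blinded staff. Uncovering the wound once that decision is made would leave those data intact. The order of dressing removal and scoring is a detail that an article may leave to the full protocol. This stands, and it is why the shares above are upper bounds. It does not remove the clash with the wording on POD 3.

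The article also does not say that later readings go unanalysed. They are collected at four times and summarised by arm, and the full protocol or analysis plan may model them. This stands too. What remains is that the article names discharge as the time point for its regression.

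The 6-day mean comes from 31 patients in ERAS and non-ERAS settings and is not labelled as open surgery. The 4-day mean is a hypothesis. The one comparison in the article of laparoscopic surgery within ERAS, 7 against 5 days, gives clearly smaller shares.

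On the baseline covariate, a fair reader would apply it only where a baseline exists. That makes it loose wording rather than an analysis error.

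**Conclusion.** The point holds as a minor one. For patients discharged within the blinded period, the rules on scoring and blinding cannot both be met, and the article selects the affected reading for its regression. On the planning assumptions, up to about 36-44% of laparoscopic and 8-14% of open patients fall in that period (29-34% against 4-10% with the 2.5-day cut; about 23-25% against 2-7% with 7 against 5 days). The figures depend on the assumed means, SD and shape; the conflict in the text does not.

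A reader might go further in two ways that the document does not support:

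- **That many laparoscopic patients will in fact rate a scar they have not seen.** The article does not say the dressing is on when the form is completed.
- **That the cosmetic difference will be diluted.** This needs covered-wound ratings to be alike in both arms and uninformative. If covered wounds were rated favourably, the difference could instead be inflated. The direction is unknown.

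The primary endpoint, the sample size and the later cosmesis readings are not affected.

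**What to change.** - In Univariate analysis, name a post-discharge reading already scheduled (10 days or later) as the analysed cosmesis score. Every such reading falls after POD 3. The 10-day reading is still counted from discharge, so on the planning means it falls at about day 14 after surgery in one arm and day 16 in the other; at 3 months or later this gap matters little.
- If the discharge cosmesis form is kept, report it descriptively only and record whether the dressing was still on. Reconcile the passages on blinding and on discharge scoring so that they say what applies to a patient who leaves by POD 3.
- State that the cosmesis model has no baseline cosmesis covariate, or that it uses the preoperative body-image score.

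The cost is a few sentences and one item on the form, with no new visit and no added patients. The small downside is losing the earliest formal comparison of cosmesis.

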#### Hospital and societal costs

The economic evaluation will include a cost-utility analysis from a Dutch societal perspective. The incremental costs per quality adjusted life year (QALY) gained will be based on utility scores from the EQ-5D [39-41]. All hospital expenses (direct and indirect) related to both interventions will be monitored. In addition, a cost questionnaire offered at the regular follow-up consultation (3, 6 and 12 months) will help assess the societal and individual costs outside health care relating to patients’ absence, impaired mobility, work, or normal daily activities. Unit prices will be based either on prices from the participating hospital financial departments or will be extrapolated using Dutch guidelines for cost calculation [45].

#### Incidence of incisional hernias

Incisional hernia after open surgery is a well-known complication of surgery, with an incidence of up to 20% after a 10-year period [46]. In patients undergoing a sigmoid resection, Anderson *et al*. found that laparoscopic resection led to a significantly lower incidence of incisional hernia compared with open surgery [47]. Furthermore, in two retrospectively analysed series of patients who received a partial hepatectomy, different types of incisions were compared. D’Angelica *et al*. reported that the common incisions used for partial hepatectomy were the Mercedes incision and extended right subcostal (ERSC) incision, and that the ERSC incision provides adequate, safe access and is associated with fewer long-term wound complications (9.8% vs 4.8%, *P* ≪ 0.001) [48]. More recently, Togo *et al*. reported frequencies of incisional hernia after median, J-shaped, right transverse incision with a vertical extension at the midline from the subumbilical region to the xiphoid process (RTVE), and reversed T incisions to be 6.3%, 4.7%, 5.4%, and 21.7%, respectively. A diagnosis of ‘no hernia’ required a minimum follow-up of 12 months [49].

To assess the incidence of incisional hernias in patients undergoing laparoscopic and open LLS, they will be contacted at a mean time of 1 year after resection to undergo ultrasonography to assess the incidence of incisional hernia.

### Study population

Every patient requiring an LLS will be identified and informed at the outpatient clinic about open and laparoscopic liver resection. Only patients meeting the inclusion and exclusion criteria will be approached for randomisation. After reading the ORANGE II trial patient information and being allowed 1 week for consideration, patients will be asked for their informed consent. All patients ineligible for randomisation will be approached for participation in the prospective registry. If patients express an explicit preference, they will be allocated to the prospective registry and interviewed to ascertain the reasons for their preferences. Personal written informed consent will be obtained for all groups. Randomisation will be carried out through the ORANGE II trial website using web-based randomisation software (TENALEA®; www.tenalea.com) (see Figure 1 for trial flow-chart).

**Figure 1 F1:**
[figure not shown]
Orange II-Trial Flowchart.

Patients will be approached for randomised inclusion if they meet each of the following inclusion criteria: require LLS; willingness to participate in the study; able to understand the nature of the study and what will be required of them; are men or non-pregnant, non-lactating women between the ages of 18 and 80 years of age; have a body mass index of between 18 and 35; and have ASA grading of I to III.

The exclusion criteria are: liver resection other than LLS; underlying liver disease; unwillingness to participate; inability to give written informed consent; and ASA grading of IV to V.

### ERAS-programme

All patients will participate in the ERAS liver programme,with a standardised peri-operative management. For daily guidelines of the pre- and postoperative care of patients undergoing liver resection (Figure 2).

**Figure 2 F2:**
[figure not shown]
Daily guideline of postoperative care of patients undergoing a hepatectomy in the ERAS programme.

### Functional recovery criteria

The evaluation of time to functional recovery will start on POD 0 and will be scored twice daily until discharge from the hospital. The discharge process starts at the pre-admission counseling session, during which any special needs of the patients will be determined (for example, homecare or social support, transport. Before admittance, any problem that could delay discharge will be identified and addressed. Patients will only be discharged when they have met the functional recovery criteria and are willing to go home. Reasons to delay discharge after functional recovery will be monitored and documented. Functional recovery criteria and LOS in hospital will be independently monitored and analysed.

#### Adequate pain control with oral analgesics

Postoperative pain will be systematically registered twice daily using the validated verbally administered 11-point numeric rating scale (NRS-11, 0 to 10) [50-53]. Members of a specialised pain team will ask patients to rate the intensity of their current pain on a scale of 0 (no pain) to 10 (worst possible pain), with pain rated as ‘mild’ (1 to 3) ‘moderate’ (4 to 6) or ‘severe’) 7 to 10 [54]. The NRS-11 seems to be better accepted by most patients and to be at least as sensitive and valid as the more traditional VAS ratings [53].

#### Tolerance of solid food

Fluid and solid food intake will be monitored and must return to normal, that is, when oral intake of water or normal food is resumed and continued for at least 24 hours. Furthermore the incidence of postoperative nausea and vomiting, which obviously influences intake, will be monitored postoperatively until day 6 using a scale ranging from 0 (no nausea) to 10 (worst possible nausea), and where necessary, be countered prophylactically by antiemetic treatment.

#### Mobility

To assess the difference between the preoperative and postoperative mobility level, the ERAS Mobility Scale (EMS) has been developed from the Groningen Activity Restriction Scale [55]. The EMS assesses 10 basic actions to compare the level of mobility before and after surgical intervention. When the patient is able to perform 8 of the 10 items, they are independently mobile. Patients will be assessed whether they are able or not to independently perform these basic actions fully. Daily the assessment will be repeated and compared with the preoperative baseline score until mobility at an independent or preoperative level is achieved.

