### Primary & secondary endpoints

The primary endpoint of the ORANGE II trial is time to functional recovery. A patient is fully functionally recovered when all of the following five criteria are satisfied: 1) adequate pain control with oral analgesia; 2) restoration of mobility to an independent level; 3) absence of intravenous fluid administration; 4) ability to eat solid foods; and normal or decreasing serum bilirubin level and international normalised ratio.

It is medically justified to discharge patients when the criteria for full functional recovery are met and if the patient is willing to go home. Secondary endpoints include postoperative LOS in hospital, percentage of readmissions, total morbidity (both general and procedure related), composite endpoint of liver-surgery-specific morbidity, QOL, body image and cosmesis, reasons for delay of discharge after functional recovery, hospital and societal costs over 1 year, and long-term incidence of incisional hernias.

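### Mobility scoring stops once the level is first reached, although functional recovery is to be scored until discharge, so recovery can be dated on an out-of-date mobility score

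*Protocol article*

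**What the plan says.** Four parts of the protocol article bear on when and how mobility enters the primary endpoint.

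- *Primary & secondary endpoints*: "A patient is fully functionally recovered when all of the following five criteria are satisfied". The second criterion is "restoration of mobility to an independent level".
- *Study design*, on the blinded ward staff: "They will record the functional recovery criteria twice daily".
- *Functional recovery criteria*, on the scoring schedule: "The evaluation of time to functional recovery will start on POD 0 and will be scored twice daily until discharge from the hospital".
- *Mobility*, on the 10-item ERAS Mobility Scale (EMS): "When the patient is able to perform 8 of the 10 items, they are independently mobile", and then "Daily the assessment will be repeated and compared with the preoperative baseline score until mobility at an independent or preoperative level is achieved".

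The other components are not written this way. For pain the article states "Postoperative pain will be systematically registered twice daily" and gives no stop at first success. Resumed oral intake has to last at least 24 hours (*Tolerance of solid food*).

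**The concern.** One component of the primary endpoint has two assessment frequencies (daily, twice daily) and two end points (first achievement, discharge). A site cannot follow both.

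Under the Mobility section, no EMS score exists after the day the level is first reached. If a patient then has a setback, the only score available when the last other criterion is met is the old one. Recovery would be dated from five criteria met at different times, not from a state in which all five hold.

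The protocol itself expects late setbacks: *Morbidity* places biliary complications, intra-abdominal abscess and liver failure in the later postoperative phase, when a patient may already have passed the mobility threshold.

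An early recovery date would also affect a secondary endpoint, the reasons for delayed discharge after functional recovery, because days of non-recovery would be counted as discharge delay. Scores that were never collected cannot be restored at analysis.

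**Working it through.** **1. The two rules side by side**

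| | Study design; Functional recovery criteria | Mobility |
|---|---|---|
| Frequency | twice daily | daily |
| Ends at | discharge (Functional recovery criteria) | first achievement of the level |
| Score available when the last other criterion is met | yes | only if mobility has not yet been reached |

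**2. When a recovery date is wrong under the Mobility rule.** Three things must happen in order: the patient reaches the level, then loses it, and is still below it when pain, fluids, food and laboratory criteria all hold. A patient who has regained mobility by then is dated correctly, even on an old score. The affected group is therefore smaller than the group with any setback.

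**3. The plan's own figure.** Inputs from *Sample size*: difference 2 days, SD 2.73, two-sided α 0.05, power 90%.
- n per arm = 2 × (1.960 + 1.282)² × (2.73/2)² ≈ 39.2, rounded up to 40. This matches the stated 2 × 40.
- Standard error at 40 per arm = 2.73 × √(2/40) = 0.610. Power = Φ(2/0.610 − 1.960) = 90.6% by the normal approximation.

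**4. Frequency alone.** Assume mobility is the last criterion and is reached at a uniformly random time between assessments. With interval g days, the mean delay in detection is g/2 and the added variance is g²/12.
- Twice daily (g = 0.5): mean delay 0.25 day; SD = √(2.73² + 0.25/12) = 2.734.
- Daily (g = 1): mean delay 0.50 day; SD = √(2.73² + 1/12) = 2.745.
- Extra delay = 0.50 − 0.25 = 0.25 day, with no stated reason to differ by arm. The required n stays at 40 per arm, and power at 40 is 90.5% and 90.3% respectively.

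**5. Stopping at first achievement.** The article gives no relapse rate, so the following are assumptions: a proportion q = 5-15% of an arm is misdated by d = 1-3 days.
- Shift in that arm's mean = q × d: from 0.05 × 1 = 0.05 day to 0.15 × 3 = 0.45 day.

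If the excess lies wholly in the open arm, the recorded difference is 2 − q × d. Power at 40 per arm, with SD held at 2.73, is:

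| Shift (days) | Recorded difference | Power |
|---|---|---|
| 0 | 2.00 | 90.6% |
| 0.05 | 1.95 | 89.1% |
| 0.20 | 1.80 | 83.9% |
| 0.45 | 1.55 | Φ(1.55/0.610 − 1.960) ≈ 72% |

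If it lies wholly in the laparoscopic arm, the recorded difference is 2.05 to 2.45 days. If both arms are affected equally, the difference in means does not move.

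**The case against.** The strongest reply is that the general rule sits in the parent section, *Functional recovery criteria*, and that the Mobility text mainly describes the scale and its threshold. The endpoint definition requires the criteria to be satisfied, in the present tense, and nothing says that an old score is carried forward. Read that way, mobility is scored until discharge and no error arises. This stands as a possible reading, but it means setting aside an explicit instruction on when to stop. A site that obeys that instruction has nothing current to score.

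A second reply is that this is a journal article, and that dating rules and case-report-form schedules belong in the full protocol. That also stands in part: the lack of a rule for lost criteria is not a finding in itself. The conflict between two stated schedules is.

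Third, the primary outcome is analysed in days (*Univariate analysis*), so a once-daily score is nearly adequate. This is accepted, and step 4 confirms it.

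Fourth, a patient who cannot mobilise would probably be kept in hospital. But the endpoint is the date of recovery, not of discharge, and *Background* reports gaps between the two.

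**Conclusion.** The conflict is real and touches the primary endpoint. The material part is the stopping rule; the frequency difference is minor. The sample size calculation is unaffected.

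The size cannot be settled from the article. The 0.05-0.45 day shift rests on assumed rates and is an upper range if q is read as the share of patients with a setback, because only those still immobile when the other four criteria hold are misdated.

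Three stronger readings are tempting and not supported:
- A reader might infer that the Mobility rule always shortens recorded recovery. The stopping rule can only bring the date forward, but once-daily scoring can put it slightly later.
- A reader might take 0.45 day, or 0.45/2 = 22.5% of the target effect, as the expected bias. It needs the top of both assumed ranges, every setback misdated, and setbacks mainly in one arm.
- A reader might infer a bias towards laparoscopy. The direction depends on which arm has more such patients. An excess in the open arm would work against finding a laparoscopic benefit.

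**What to change.** Reconcile the Mobility section with *Study design* and *Functional recovery criteria*: score the EMS on the recovery-assessment schedule until discharge, without stopping at first achievement. Add one statement to the endpoint definition: functional recovery is dated at the first assessment at which all five criteria currently hold, with food judged over its stated 24 hours and the laboratory criteria on the latest available values.

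In the same edit, align the required level, since the Mobility section accepts an independent or a preoperative level and the endpoint definition names only an independent one.

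The cost is a 10-item able/not-able checklist repeated for a few more days per patient. The change concerns outcome measurement only. It does not address a setback after all five criteria have been met together; such a patient would keep the earlier date.
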